#### Magnetic Resonance Imaging

In this study, a GE Discovery MR750 1.5T MRI scanner will be used for imaging. During the test, the participant will be placed in a supine position, with their head held stable with a fixation frame. Moreover, the participant will be asked to wear earplugs to reduce stimulation due to equipment noise, so that the participant can relax as much as possible. First, a routine sequence axial scan will be performed to exclude organic lesions in the brain or the presence of artifacts; GABA and Glu experimental data will be collected again if there is no definite abnormality in the brain.

### Safety Evaluation

Adverse events during the study will be recorded and reported, and the patients will be treated in a timely and reasonable manner. The researchers will explain to the patients that they (or their families) are required to truthfully communicate the changes in their condition after treatment. The physicians will avoid guiding questions. During the observation of a curative effect, the researchers will pay attention to identify any adverse reactions.

Adverse events such as bleeding, hematoma, fainting, pain at the acupuncture site, and elevated blood pressure caused by acupuncture at any time will be recorded. Regardless of whether the adverse reactions or adverse events are related to the treatment method of this study, they will be recorded in detail. When these conditions occur, the patients will be recorded and treated properly in time until they completely return to normal, and the causes of adverse reactions will be analyzed.

### Data Management

The researchers will fill in the collected data into the case report forms according to the requirements of the research program. At the end of the study, the researchers will submit the case report forms of all patients included in this study to the data management center. These case report forms are required to be complete and signed. An internal data consistency check will be performed on all case report forms. Any inconsistencies identified will be logged, and a formal query will be generated and sent to the principal investigator for clarification and resolution.

### Sample Size and Statistical Methods

The main outcome measure of this study will be the total PSQI score at 4 weeks after treatment. The sample size was calculated on the basis of the expected difference between the test acupuncture group and the conventional acupuncture group in this index.

The expected effect size was determined as follows: studies have shown that acupuncture can significantly reduce PSQI scores compared with conventional therapy, with a combined mean difference of 2.0 to 3.5 points [16]. With reference to an RCT of similar design [17], we conservatively estimated that the mean difference (Δ) of PSQI between the 2 groups after treatment was 2.5 points, and the combined SD was approximately 4.0 points. According to this calculation, the standardized effect size is 0.625 (Δ/SD=2.5/4.0). Using G*Power software (version 3.1; Heinrich-Heine University Dusseldorf), setting α=.05 (bilateral) and test efficiency (1-β)=80%, according to a 1:1 distribution, the minimum sample size of each group was calculated to be 43. Considering a dropout rate of approximately 10%, 48 patients will be included in each group, and a total sample size of 96 patients was finally determined.

SPSS software (version 22.0; IBM Corp) will be used to analyze the collected data. All data will be expressed as mean (SD). For measurement data of the 2 groups, normally distributed data will be analyzed by independent 2-tailed *t* test and paired 2-tailed *t* test. If the data are not normally distributed, the Mann-Whitney rank sum test will be used. One-way ANOVA will be used for comparison between groups. Count data will be analyzed using a chi-square test, and rank data will be compared using the rank sum test and other analysis methods. A *P* value of ≤.05 will be considered statistically significant. To control for potential confounding, the use of concomitant medications and measures derived from sleep diaries will be incorporated as covariates into a generalized linear model for sensitivity analysis of the primary outcomes.

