**Figure 1. F1:**
[figure not shown]
Study flowchart. DBAS-16: 16-item Dysfunctional Beliefs and Attitudes About Sleep scale, GABA: γ-aminobutyric acid, Glu: glutamic acid; HRV: heart rate variability; ISI: Insomnia Severity Index; MRI: magnetic resonance imaging; PSG: polysomnography; PSQI: Pittsburgh Sleep Quality Index; SF-36: 36-item Short Form Health Survey.

**Table 1. T1:** Schedule of study assessments and outcome measures.

Research stage	Before treatment	Treatment stage	Follow-up stage
Assessment	First	Second	Third
Time (weeks)	0	4	8
Informed consent	✓	—^a^	—
Inclusion/exclusion criteria	✓	—	—
Demographic data	✓	—	—
Vital signs	✓	—	—
Medical history record	✓	—	—
Physical examination	✓	—	—
Medication situation	✓	—	—
Indicator of mechanism			
HRV^b^	✓	✓	✓
PSG^c^	✓	✓	✓
MRI^d^	✓	✓	—
Primary outcome indicator			
PSQI^e^	✓	✓	✓
SF-36^f^	✓	✓	✓
Secondary outcome indicator			
ISI^g^	✓	✓	✓
DBAS-16^h^	✓	✓	✓
GABA^i^	✓	✓	—
Glu^j^	✓	✓	—
Safety evaluation	✓	✓	✓

a Not applicable.

b HRV: heart rate variability.

c PSG: polysomnography.

d MRI: magnetic resonance imaging.

e PSQI: Pittsburgh Sleep Quality Index.

f SF-36: 36-item Short Form Health Survey.

g ISI: Insomnia Severity Index.

h DBAS-16: 16-item Dysfunctional Beliefs and Attitudes About Sleep scale.

i GABA: γ-aminobutyric acid.

j Glu: glutamic acid.

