**Exclusion criteria (patients who meet any one of the following criteria will be excluded)**
Patients with insomnia caused by a variety of organic diseases or neurological or psychiatric disordersPregnant or lactating patients or those with a drug allergyPatients with more serious primary diseases such as cardiovascular and cerebrovascular diseases, gastrointestinal diseases, endocrine system diseases, or psychiatric disordersPatients with coagulation dysfunction and bleeding tendency

The baseline assessment will be performed by the same physician, and the results will be recorded in detail in the case report form. All participants will receive treatment for 4 weeks and undergo follow-up observation after treatment. The evaluation will be done at 3 time points: before treatment, after 4 weeks of treatment, and at 4 weeks after end of treatment. Each participant will receive a schedule of treatment dates and a schedule of follow-up appointments developed by research assistants who will be blinded to the grouping information.

In addition, all participants will be required to keep a sleep diary throughout the treatment and follow-up periods, recording the date of each insomnia episode, the length of time required to fall asleep, the number of times they wake up at night, the difficulty of falling asleep again, and the subjective feelings after waking up in the morning. Moreover, they will be asked to include sleep-related details as well as the name, dose, and time of use of other drugs (such as sleeping pills) during the trial and their own feelings after taking the drug.

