##### Quality of Life Assessed Using the 36-Item Short Form Health Survey

The patients will be evaluated using the 36-item Short Form Health Survey (SF-36) at each observation point. The SF-36 is a general scale developed by the American Medical Research Group to evaluate the quality of life. It is widely recognized and used worldwide. This scale has 8 dimensions to evaluate health-related quality of life, which belong to 2 categories of physical health and mental health, namely physiological function, role-physical, bodily pain, general health, vitality, social function, role-emotional, and mental health. In addition, the SF-36 scale includes another indicator, health change, which is used to evaluate health changes over the past year.

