This study incorporates a parallel cohort of healthy controls to establish normative baselines for HRV and relevant neurochemical markers. These reference values will enable the quantitative assessment of the severity of ANS dysfunction in patients with insomnia and provide a benchmark for evaluating postintervention recovery. This comparative design strengthens the robustness of the findings and supports a multidimensional evaluation of treatment efficacy.

To comprehensively capture both objective and subjective dimensions of sleep and autonomic function, the primary outcome indicators include the PSQI and SF-36. The secondary outcome indicators include the ISI and DBAS-16 as well as GABA and Glu levels. These 2 neurotransmitters were selected as biomarkers because they play an important role in sleep-wake regulation and the high arousal state characterized by primary insomnia. Assessing these neurochemicals will help to elucidate the mechanisms underlying treatment response.

Methodologically, the trial employs a single-blind, randomized design with block randomization to minimize selection bias. The sample size was determined by an a priori power calculation to ensure adequate statistical power, and all acupuncture procedures will be performed adhering to a strict standardized protocol to maintain treatment fidelity across participants. Focusing exclusively on patients with the liver depression-spleen deficiency pattern will reduce clinical heterogeneity, allowing a more precise investigation of acupuncture mechanisms within this defined TCM syndrome framework.

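### The trial is sized on PSQI alone but lists PSQI and SF-36 as primary, and the deciding visit can be read as week 4 or week 8

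*Protocol article*

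**What the plan says.** On which outcome is primary:

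- Sample Size and Statistical Methods names one outcome: "The main outcome measure of this study will be the total PSQI score at 4 weeks after treatment". The expected difference, the SD and the sample size all refer to this score.
- The same section closes its analysis text in the plural, with a "sensitivity analysis of the primary outcomes".
- Table 1 has a row group headed "Primary outcome indicator" that contains both PSQI and SF-36, each ticked at weeks 0, 4 and 8.
- Primary Outcome Measures has one subsection for PSQI and one for SF-36. Of the latter it says: "The patients will be evaluated using the 36-item Short Form Health Survey (SF-36) at each observation point". It also says "This scale has 8 dimensions to evaluate health-related quality of life", groups these into a physical and a mental category, and adds a health change item.
- The Discussion (Proposed Mechanism and Empirical Testing) states that "the primary outcome indicators include the PSQI and SF-36".

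On the visit, the text after the eligibility criteria in Participant Recruitment gives three assessments: "before treatment, after 4 weeks of treatment, and at 4 weeks after end of treatment". Table 1 numbers them weeks 0, 4 and 8.

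On the threshold, the statistical section gives a single significance level, P≤.05.

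**The concern.** A confirmatory trial needs one statement of what counts as success: which score, at which visit, and, if there is more than one score, by what rule. The article gives two accounts of the score. No sentence makes SF-36 subordinate to PSQI, and none says whether a significant result on either would suffice or both are needed.

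The visit phrase in the sample-size section matches neither of the two post-baseline visits as the article words them elsewhere, and it fits both. The two visits answer different questions. Week 4 shows the effect at the end of the course. Week 8 shows whether it lasts, and the Conclusion treats the follow-up as the evidence on long-term effect. A difference present at week 4 may have gone by week 8, so the choice can change the result.

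If this stays open until the data are seen, the choice of score and visit can follow the results. Neither the 5% error rate nor the stated power would then be secure.

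**Working it through.** **1. The plan's own sample size.** Inputs from Sample Size and Statistical Methods: Δ = 2.5 points, SD = 4.0, two-sided α = .05, power 80%, allocation 1:1, dropout 10%.

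- Normal approximation: n = 2(z₀.₉₇₅ + z₀.₈₀)²(SD/Δ)² = 2 × (1.960 + 0.842)² × (4.0/2.5)² = 2 × 7.85 × 2.56 = 40.2, so 41 per group.
- Exact noncentral t: 42 per group. The plan states 43.
- Dropout: 43/0.9 = 47.8, so 48 per group and 96 in total, as stated.

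The arithmetic is sound. At 43 evaluable per group the power for PSQI is 82%. No SF-36 quantity enters the calculation.

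**2. If either instrument may carry the trial.** Take PSQI plus one SF-36 score, each tested at .05. The article gives no correlation between the two, so a range is assumed.

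- Independent tests: 1 − 0.95² = 9.75%.
- Correlation 0.5 (simulated bivariate normal statistics, 400,000 draws, share with at least one |Z| > 1.96): 9.1%.
- Correlation 0.7: 8.4%.

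Restoring 5% by Bonferroni means α = .025 for each. For the PSQI effect, 80% power then needs 50 evaluable per group by the exact t calculation. With dropout that is 50/0.9 = 55.6, so 56 per group and 112 in total. At the planned 43 evaluable per group, power falls to 73%.

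**3. If both must succeed.** Each test can stay at .05 and the overall error rate does not exceed 5%. Joint power cannot exceed the 82% for PSQI alone. How far below it falls cannot be computed, because the article gives no SF-36 effect or SD.

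**4. Outer bound, for a rule that the article does not state.** If any one of several scores counted, with independent tests:

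| Hypothetical set of tests | Number | 1 − 0.95ᵏ |
|---|---|---|
| PSQI, SF-36 physical, SF-36 mental, one visit | 3 | 14% |
| PSQI and 8 SF-36 dimensions, one visit | 9 | 37% |
| The same 9 scores at both visits | 18 | 60% |

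Positive correlation lowers these. At an assumed 0.7 the last two become 20% and 28%.

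**5. The visit.** Read literally, the sample-size phrase points to week 8. Other text leans to week 4: the assumed 2.5-point difference is placed only after treatment, with no week, and Study Setting and Design speaks of evaluation in the fourth week of the treatment period. Neither indication settles it.

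**The case against.** The best defence is that the statements can be fitted together. PSQI is singled out as the main outcome and carries the sample size, and SF-36 then sits beside it as a supporting member of a primary group. That is a fair reading and may be the intended one. But the article never states that ranking, and its table, outcome headings and Discussion give the two equal standing.

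A second defence is that SF-36 scoring and any multiplicity rule may be in the statistical analysis plan or full protocol, which are not shown. This stands. The lack of an adjustment, or of a chosen SF-36 score, is not a fault in a condensed article. The conflict over what is primary is of a different kind, because it lies between statements that the article does make.

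A reader might go further and infer that the trial could be declared positive on any SF-36 dimension at either visit, with a false-positive risk of up to 60%. The documents do not support that. No section says that one significant score is enough. Measuring at every visit is a schedule, not a plan to test at every visit. The unclear phrase leaves one visit to be identified and does not claim both. If both instruments must succeed, there is no inflation at all.

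**Conclusion.** The point holds as an inconsistency in the current text. One section names and sizes a single primary outcome, while the table, the outcome section and the Discussion list two, and the deciding visit can be read as either of two study weeks. It should be resolved before analysis because it determines what counts as success.

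The size depends on a decision rule that the article leaves open. If either PSQI or one SF-36 score suffices, the error rate is about 8–10% instead of 5%, under correlations that are assumed. If both are required, the error rate holds and joint power is unknown. The 37% and 60% figures are a hypothetical worst case, and the conclusion does not rest on them. The sample-size calculation for PSQI is not in question.

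**What to change.** Before any analysis, by a dated amendment:

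- declare total PSQI at one visit, given by study week (week 4 or week 8), as the sole primary endpoint;
- move SF-36 to the secondary outcomes;
- make Table 1, Primary Outcome Measures, Sample Size and Statistical Methods and the Discussion agree, and put the plural reference to primary outcomes in the singular.

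The 96 patients and α = .05 then stand unchanged. Keeping both instruments as primary is possible, but it needs a stated success rule. An either-suffices rule with Bonferroni would call for about 112 patients. A both-required rule would need an SF-36 score and a sample-size basis for it.

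The cost is modest. SF-36 loses a primary label for which it was never powered. Ethical Considerations requires changes to the main protocol to go to the ethics committee, and recruitment is under way (40 participants enrolled by December 2025), so the amendment should record its date and reason. Because analysis is planned only after recruitment closes, there is still time.

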## Results

This study was funded in November 2023. Recruitment and data collection began in January 2024. The results will be shared with participants, researchers, and the public via conferences, publications, and online platforms. The findings will be submitted to a peer-reviewed journal. Participant recruitment is underway and will continue until the target sample size of 96 patients with primary insomnia of liver depression and spleen deficiency type and 48 healthy controls is reached. Participant recruitment is scheduled to be completed by the end of 2026. Each enrolled patient will undergo the 4-week intervention followed by a 4-week follow-up period as per the study protocol. As of December 2025, a total of 40 participants have been enrolled, of whom 4 have withdrawn. Data collection is expected to conclude by the end of 2026, with full data analysis and manuscript preparation completed by summer 2027.

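### The one-visit t test named for total PSQI leaves a patient's other PSQI scores unused, and its estimate is biased if loss is related to PSQI and differs between arms

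*Protocol article*

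**What the plan says.** Sample Size and Statistical Methods fixes one outcome at one time: "The main outcome measure of this study will be the total PSQI score at 4 weeks after treatment". For the comparison it states that "normally distributed data will be analyzed by independent 2-tailed *t* test and paired 2-tailed *t* test", with the fallback "If the data are not normally distributed, the Mann-Whitney rank sum test will be used". Loss to follow-up is reflected in the size of the trial: "Considering a dropout rate of approximately 10%, 48 patients will be included in each group". The only sensitivity analysis takes concomitant medication and sleep-diary measures, which "will be incorporated as covariates into a generalized linear model for sensitivity analysis of the primary outcomes"; its stated purpose is control of confounding.

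PSQI is nevertheless measured repeatedly. Table 1 schedules it at weeks 0, 4 and 8, and the Participant Recruitment section says "The evaluation will be done at 3 time points: before treatment, after 4 weeks of treatment, and at 4 weeks after end of treatment".

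Two passages bear on loss. The overview under Interventions lets a participant with severe insomnia, or one who needs drugs that may act on the central nervous system, be recorded either as a major deviation or as withdrawn. It adds that medication data of those who need drugs will enter the analysis as a covariate. The Results section reports "As of December 2025, a total of 40 participants have been enrolled, of whom 4 have withdrawn".

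**The concern.** An independent t test or a Mann-Whitney test at one visit takes one value per patient. A patient without PSQI at that visit contributes nothing unless a value is supplied from elsewhere, even if the trial holds that patient's baseline and week-4 scores. The generalized linear model adds covariates for patients who have the outcome. It does not bring back those who lack it.

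This matters most if the patients who leave differ in PSQI from those who stay, and do so to a different extent in the two arms. The article makes the first condition plausible, because severe insomnia can itself be recorded as withdrawal. The second cannot be excluded, because the arms are needled at quite different sites: the neck in one, and the scalp, trunk, hand and foot in the other. An arm that loses more of its poor sleepers would then look better than it is.

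**Working it through.** **The plan's own figures.** Inputs from Sample Size and Statistical Methods: difference 2.5, SD 4.0, two-sided alpha 0.05, power 80%, ratio 1:1.
- Normal approximation: 2 × (1.96 + 0.8416)² / 0.625² = 40.2, so 41 per arm.
- Noncentral t: 42 per arm (power 80.8%); 43 gives 81.7%.
- Mann-Whitney with relative efficiency 0.955: 44 per arm; 43 gives 79.9%.
- The stated 43 is within two patients of all of these. 43 / 0.9 = 47.8, so 48 per arm and 96 in total. The figures reproduce.
- Unequal numbers alone cost little: 48 against 38 analysed gives 81.2% power.

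**When the one-visit estimate is biased.** Let m be the proportion lost in an arm, and let k be how many points worse the lost patients would have scored than those who stay. The mean of those who stay is then the full mean minus m × k. The observed control-minus-test difference is

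2.5 − (m_control × k_control − m_test × k_test).

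| Loss test / control | k | Observed difference |
|---|---|---|
| any | 0 in both arms | 2.5 |
| 10% / 10% | same in both arms | 2.5 |
| 5% / 15% | 2 in both arms | 2.5 − 0.10 × 2 = 2.3 |
| 5% / 15% | 4 in both arms | 2.5 − 0.10 × 4 = 2.1 |
| 0% / 20% | 4 in both arms | 2.5 − 0.20 × 4 = 1.7 |
| 10% / 10% | 0 test, 4 control | 2.5 − 0.10 × 4 = 2.1 |

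Unequal rates without a link to PSQI do no harm. Equal rates can still bias the result if the reasons for leaving differ by arm.

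**Simulation.** Assumptions not in the documents: main visit week 8; every patient has a week-4 score; loss after week 4 follows a logistic model on that score with log-odds 1 or 2 per SD. From the plan: SD 4, 48 per arm, true difference 2.5.

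1. Weeks 4 and 8 only, correlation 0.6 to 0.8, 4,000 trials per setting. At 5% against 15% loss the t test gives 2.07 to 2.30, and with the rates reversed 2.73 to 2.92. The bias is therefore 0.20 to 0.43 in one direction and 0.23 to 0.42 in the other. The repeated-measures likelihood estimate stays at 2.47 to 2.52.
2. Baseline added (correlation 0.4 with both later visits; weeks 4 and 8 correlated 0.7), 4,000 trials per setting. At 5% against 15% the t test gives 2.28 to 2.14 with power 76% to 73%; an estimate using weeks 0 and 4 gives 2.52 to 2.50. At 0% against 20% the t test gives 2.00 to 1.74 with power 64% to 53%. With no true difference, the type I error is 6.3% to 7.2% (5% against 15%) and 8.3% to 14.6% (0% against 20%). Loss unrelated to PSQI leaves the t test at 2.49 to 2.51 in every loss pattern.

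**Precision with equal 10% loss.** Neither method is biased.
- Without baseline (set-up 1), the standard error is 0.86 to 0.89 for the t test and 0.83 to 0.84 for the likelihood estimate. Taking z = 2.5 / SE, 2.5 / 0.877 gives about 81% power and 2.5 / 0.838 about 85%.
- With set-up 2's correlations and a likelihood estimate adjusted for baseline, it falls from about 0.83–0.87 to 0.77–0.79. Much of that fall is due to baseline: with no loss at all, 4 × √(2/48) = 0.816, and 0.816 × √(1 − 0.4²) = 0.748. The gain from recovering lost patients alone is small.

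**Loss so far.** 4 / 40 = 10%, exact 95% interval 2.8% to 23.7%. The article gives no split by arm or reason.

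**The case against.** The best defence is that the article names no analysis set and no missing-data rule, and that both are commonly left to a statistical analysis plan. That stands. A reader might infer that the trial plans an analysis of completers, but the article never says so, and a t test can be run on imputed data. The absence of an imputation rule here is not the finding. The finding concerns the method that is stated.

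A reader might also infer that unequal loss biases the result by itself. It does not: at 0% against 20% loss unrelated to PSQI, the estimate stays at about 2.5. Nor does outcome-related loss alone suffice if it works equally in both arms. Nor is the dropout sentence an error; it shows only that loss is expected.

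Three further objections have weight.
- The main visit is unclear. The wording is close to the one used for the visit 4 weeks after treatment ends (week 8), but it can be read as the end of the 4-week treatment. On that reading a lost patient usually has only a baseline score, and a repeated-measures model recovers less.
- The simulated loss always follows an observed week-4 score, which favours the likelihood model. Patients who leave during treatment would be recovered far less well.
- Differential outcome-related loss is possible but not shown. Both arms receive active acupuncture on the same schedule, and the withdrawal rule also allows a patient to be kept as a deviation.

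**Conclusion.** The point holds in conditional form. The stated between-group test uses PSQI at one visit and ignores the scores at the other two, and the covariate model does not repair this. If loss is related to PSQI and differs between arms, the estimate is biased. At an assumed 5% against 15% loss after week 4 the bias is about 0.2 to 0.45 points on a true 2.5 (largest simulated value 0.43), in either direction according to which arm loses more. Without such a difference the cost is precision only.

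These sizes rest on assumed correlations, an assumed loss mechanism and week 8 as the main visit. The article supplies only the 2.5, the 4.0, the 48 per arm and the expected 10%. The change is worth making because the data are already scheduled and the sample size is unaffected.

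**What to change.** In Sample Size and Statistical Methods, amend the t-test sentence:

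1. State whether the main visit is week 4 or week 8.
2. Make the primary analysis of total PSQI a likelihood-based repeated-measures model in all randomised patients, in their assigned arm, with the arm contrast at the main visit as the result. Either take weeks 0, 4 and 8 as responses with baseline means constrained equal across arms, or take weeks 4 and 8 as responses with baseline PSQI as covariate. The first also keeps patients with no score after baseline; the second drops them.
3. Keep the one-visit t test as a sensitivity analysis and add one that allows data to be missing not at random.

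The cost is wording and slightly more analysis work. SPSS, the stated software, can fit a mixed model, and 48 per arm stands. The model relies on data being missing at random given the observed PSQI, which is a weaker assumption than the t test needs on observed cases. Analysis is to follow the end of recruitment, projected for December 2026, so the change can be made before any results are seen.

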### Outcome Measures

#### Primary Outcome Measures

##### Sleep Quality Assessed Using the Pittsburgh Sleep Quality Index

The patients will be assessed using the Chinese version of the Pittsburgh Sleep Quality Index (PSQI) questionnaire at each observation point, and the clinical efficacy will be assessed. The questionnaire consists of 19 self-evaluation items and 5 other evaluation items. Only the 19 self-evaluation questions will be scored, which comprise 7 factors, each scored on a scale of 0 to 3 points (0: no difficulty, 3: serious difficulty). The sum of all factor scores ranges from 0 to 21, with a total score of 21 indicating serious difficulty in all respects. The reference values for adult sleep quality problems in China are as follows: PSQI ≥8 indicates poor sleep quality, whereas PSQI ≤7 indicates good sleep quality; the higher the score, the worse the sleep quality.

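### The between-arm PSQI comparison leaves out baseline PSQI, which is measured on every patient before randomisation; the test is valid but gives up precision

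*Protocol article*

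**What the plan says.** All of the analysis text is in the protocol article under Sample Size and Statistical Methods.

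- Endpoint: "The main outcome measure of this study will be the total PSQI score at 4 weeks after treatment".
- Between-arm test: "For measurement data of the 2 groups, normally distributed data will be analyzed by independent 2-tailed" t test. The paired t test named alongside it is a within-group comparison, and the one-way ANOVA named shortly after carries no covariate.
- Fallback: "If the data are not normally distributed, the Mann-Whitney rank sum test will be used".
- The only covariate model: "the use of concomitant medications and measures derived from sleep diaries will be incorporated as covariates into a generalized linear model for sensitivity analysis". Baseline PSQI is not among the covariates named.

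The baseline score will exist for every patient. Under the PSQI outcome heading: "The patients will be assessed using the Chinese version of the Pittsburgh Sleep Quality Index (PSQI) questionnaire at each observation point". Under Participant Recruitment: "The evaluation will be done at 3 time points: before treatment, after 4 weeks of treatment, and at 4 weeks after end of treatment". Table 1 marks PSQI at weeks 0, 4 and 8. Randomization and Blinding says that the baseline assessment is complete before the allocation envelope is opened, so baseline PSQI is a true pre-randomisation covariate.

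**The concern.** When an outcome is also measured before randomisation, adjusting for the baseline value removes the part of the outcome variance that it explains. The eligibility criteria set no minimum PSQI, and the randomisation uses blocks of 4 with no stratification factor named. Baseline severity may therefore vary and may differ between arms by chance. An unadjusted comparison carries all of that variation in its standard error.

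The existing covariate model does not fill the gap. It is a sensitivity analysis only, and its named covariates (concomitant medication and diary measures) are recorded during treatment and follow-up, so treatment itself may affect them.

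The normality rule is a second weakness in the same sentences. The trial is sized on a difference in means. If a check on the data sends the analysis to Mann-Whitney, the test no longer addresses that difference, and which question is answered is decided after the data are seen.

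**Working it through.** **Inputs from the document** (Sample Size and Statistical Methods): difference 2.5 points; SD 4.0; two-sided α 0.05; power 80%; 1:1 allocation; 43 per arm, or 48 after 10% dropout. The section also cites a "combined mean difference of 2.0 to 3.5 points", so 2.0 is taken as the low case.

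**Assumptions** (not in the documents): the correlation r between baseline and post-treatment PSQI is 0.3 to 0.6, and the SD of 4.0 is a raw post-treatment SD.

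**Step 1: the plan's own figure.** Standardised effect 2.5/4.0 = 0.625. The normal approximation gives 41 per arm and the noncentral t gives 42, both close to the stated 43. Dropout: 43/0.9 = 47.8, rounded up to 48. The plan's figure reproduces within two patients per arm.

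**Step 2: the unadjusted test at 43 per arm.** Standard error = 4.0 × √(2/43) = 0.863. Half-width = 1.989 × 0.863 = 1.72 points (t quantile, 84 df). Noncentral t power is 81.7% for 2.5 points and 63.0% for 2.0 points.

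**Step 3: adjusting for baseline.** Residual SD = 4.0 × √(1 − r²), with one further degree of freedom spent (83 df). Equivalent unadjusted size = 43/(1 − r²).

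| r | Variance removed | Residual SD | Power, 2.5 points | Power, 2.0 points | Half-width | Equivalent n per arm |
|---|---|---|---|---|---|---|
| none (t test) | – | 4.00 | 81.7% | 63.0% | 1.72 | 43 |
| 0.3 | 9% | 3.82 | 85.1% | 67.1% | 1.64 | 43/0.91 = 47.3 |
| 0.5 | 25% | 3.46 | 91.1% | 75.4% | 1.49 | 43/0.75 = 57.3 |
| 0.6 | 36% | 3.20 | 94.7% | 81.7% | 1.37 | 43/0.64 = 67.2 |

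**Step 4: the gain in patients.** 47.3 − 43 = 4.3 and 67.2 − 43 = 24.2, so about 4 to 24 per arm.

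**Step 5: a weak correlation.** At r = 0.2 power for 2.5 points is 83.2%, still above 81.7%. The lost degree of freedom does not outweigh the gain even there.

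**The case against.** The strongest reply is that nothing here is an error. Under 1:1 randomisation the t test is valid, and the sample size was built on the same unadjusted comparison, so plan and test agree. That stands.

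Four stronger readings are tempting, and the documents do not support them.

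- *The result would be biased by baseline imbalance.* Chance imbalance is ordinary sampling variance, and the t test's standard error already allows for it. Adjustment reduces that variance; it does not remove a bias.
- *The trial is too small because of the t test.* It has 82% power for its own assumptions. The 63% at 2.0 points comes mainly from sizing on 2.5. Adjustment lifts it to only 67% at r = 0.3 and 75% at r = 0.5, and passes 80% only at the top of the assumed range.
- *Adjustment is worth 47 to 67 patients per arm.* That is the equivalent total per arm, not the gain.
- *The comparison is at week 4.* The endpoint sentence could mean the end of the 4-week treatment or 4 weeks after it ends, and the evaluation schedule has both visits. The correlation with baseline may differ between them.

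The size of the gain is also open to challenge. The documents do not give r, and because all patients must meet insomnia criteria, a narrow baseline range could hold it down. Nor do they say whether 4.0 is a raw or a change-score SD. If it is a change-score SD, the power and half-width figures do not apply as they stand, although the proportional variance reduction of r² against an unadjusted post-treatment comparison still does.

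An unseen analysis plan may add covariates, but the protocol article itself names the test, and that choice is what is questioned here.

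**Conclusion.** The point holds as a recommendation on efficiency, not as a finding of error. The direction is secure: baseline PSQI is available before allocation, and using it improves precision for any correlation clearly above zero. The size is conditional on the two assumptions in the working. Within them the gain ranges from modest (3.4 percentage points of power for 2.5 points at r = 0.3) to substantial (13 percentage points at r = 0.6).

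The normality switch is a separate reason to change the same sentences and does not depend on r: the estimand should not turn on a check of the data.

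**What to change.** Replace the between-arm test for the primary outcome with wording such as: *The primary analysis is a linear model (ANCOVA) of total PSQI at the primary visit on randomised arm and baseline PSQI. The adjusted mean difference and its 95% confidence interval will be reported whatever a normality check shows. The unadjusted t test or the rank test is a sensitivity analysis.* State in the same place whether the primary visit is week 4 or week 8.

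Baseline adjustment may be extended to the other outcomes measured at week 0, each with its own baseline. Skewed measures such as the HRV spectral powers and LF/HF should be log-transformed first; an untransformed linear model is not justified for them.

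Cost: no new data, visits or patients, and the sample size stands. It does need a protocol amendment. Ethical Considerations sends changes to the main protocol to the ethics committee, and recruitment is under way (40 participants by December 2025). Because the Abstract places data analysis after recruitment is complete, the change can still be specified in advance.
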